## Abstract

**Background:**

Research on the effect of acupuncture has been limited. Whether the effect of acupuncture is equivalent to placebo has been the focus of debate in this field. This study will explore the specific and non-specific effects of acupuncture for knee osteoarthritis (KOA) by functional magnetic resonance imaging (fMRI).

**Methods and design:**

Ninety participants diagnosed with KOA will be randomly divided into the acupuncture group, sham acupuncture group, and waiting list group in a ratio of 1:1:1. Except for the waiting list group, the other participants will receive acupuncture or sham acupuncture three sessions per week for 4 weeks respectively. The primary outcome will be the response rate which is defined on an individual basis as at least a 2-point decrease in the numerical rating scale (NRS) of pain at the end of intervention period compared with the baseline. fMRI scans will be performed at baseline and the end of the intervention period to examine the response of various brain regions. The secondary outcomes will include the Western Ontario and McMaster Osteoarthritis Index (WOMAC), State-Trait Anxiety Scale-State Anxiety Subscale (STAI-S), and Stanford Expectations of Treatment Scale (SETS). Pearson’s correlation coefficient will be performed to investigate the changes in brain activity and clinical variables.

**Discussion:**

The results of our study will help to evaluate the specific and nonspecific effects of acupuncture combined with clinical and brain function changes based on KOA.

**Trial registration:**

Chinese Clinical Trial Registry ChiCTR1900025799. Registered on 9 September 2019.

## Background

The therapeutic effect of the intervention may be the result of its specific effect and nonspecific effect [1]. In this progress, the nonspecific effect of treatment (e.g., acupuncture) may be caused by accidental intervention factors, such as expectation and emotion [2]. The term “placebo effect” is thought to partially explain the nonspecific effects of these treatments [3]. The cumulative evidence suggested that the placebo effect was a real psychobiological event that was attributable to the interaction between the participant, clinician, and treatment environment in the overall treatment context [4–6]. However, the clinical impact of the placebo is largely overlooked, especially that the placebo effect in a randomized controlled trial (RCT) is usually subtracted from the treatment effect [7].

In recent years, accumulating evidences from RCTs suggest that acupuncture was effective compared with no treatment [8]. At the same time, some large randomized clinical trials comparing acupuncture with sham or placebo acupuncture found that the therapeutic effect of acupuncture is greatly reduced, indicating that the nonspecific effect (placebo effect) of acupuncture may play a part role [9–11]. A randomized controlled trial attributed the acupuncture effect to a powerful placebo effect [12]. Although previous studies supported that the holistic effect of acupuncture included specific and nonspecific effects [13, 14], but the proportion of the effects and their determinants were still unclear. Understanding comprehensively the effect of acupuncture and integrating the nonspecific effects into clinical practice (for example, improving treatment expectations) may help to optimize the holistic effect [15]. Therefore, in the selection and implementation of interventions, it becomes increasingly important that nonspecific be separated from specific effects. In order to evaluate the importance of nonspecific effects, the sham acupuncture was used as the control to further distinguish the acupuncture effect in this study design.

Along with the use of neuroimaging techniques in pain research, there are growing evidences that the neural markers of the brain can predict pain perception and response to drugs or non-drug therapy [16–18]. Since neuroimaging may provide objective markers of the effects of treatments on the organism, it enables a more nuanced and biology-based interpretation of RCT outcomes, where active treatment and inert placebo treatment might be differentiated at the brain circuit level [19]. Pascal et al. showed that clinical placebo response had biological underpinnings by using functional connectivity to predict placebo responders and non-responders. The differences in the whole-brain map identified four brain regions that distinguished placebo responders from non-responders; the right medial frontal gyrus (r-MFG) was the most significant, followed by posterior cingulate cortex (PCC), anterior cingulate cortex (ACC), and the right secondary somatosensory and primary motor cortex (r-s2/M1) [20]. Another RCT study examined the effects of placebo drugs on brain activity in participants with chronic back pain; it found that the placebo analgesia depended on the structure and function of the brain [21]. In recent years, functional magnetic resonance imaging (fMRI) has been used to investigate the central regulatory mechanism of acupuncture effect [22, 23]. Previous neuroimaging studies showed that acupuncture could regulate the functional connections of pain-related networks [24–28]. During analgesia, acupuncture could restore the critical brain areas to change the attention and memory associated with pain, especially the periaqueductal gray (PAG), medial frontal cortex (MFC), and bilateral hippocampus (Hpc) [29]. However, the brain activity regulated by placebo acupuncture is usually neglected, which leads to insufficient evidence to identify the neurological mechanisms triggered by the specific and nonspecific effects of acupuncture.

The pain was the most common research topic in acupuncture-related studies published from 1994 to 2014, accounting for about one third of the total publications [30]. A cross-sectional study found that among the common acupuncture adaptation diseases, 5 of the top 10 diseases were related to pain [31]. Knee osteoarthritis (KOA) is high-prevalence chronic osteoarthritis with knee pain and functional limitation [32–34]. The positive response of placebo treatment is a recognized phenomenon in the chronic pain, and the analgesic effect is often comparable to active treatment [35]. For these reasons, KOA is an appropriate model to study the specific and nonspecific effects of acupuncture.

The purposes of this study are to (1) investigate the cerebral mechanism of the specific (true acupuncture vs sham acupuncture) and nonspecific effects (sham acupuncture vs waiting list) of acupuncture based on the brain activities by using fMRI and (2) investigate the proportion of specific and nonspecific effects in acupuncture treatment.

## Methods and design

### Study design

This is a randomized controlled, parallel study to explore whether specific and nonspecific effects of acupuncture regulate certain brain functional connectivity, respectively. Ninety participants will be recruited in the study, with an average of 30 in each group. Clinical data measurements and fMRI scans will be evaluated at baseline and the end of treatment (Figs. 1 and 2). The study has been approved by the ethical committees of Dongzhimen Hospital Affiliated to Beijing University of Chinese Medicine (NO: DZMEC-KY-2017-53-02) and registered in the Chinese Clinical Trial Registry (NO: ChiCTR1900025799). The protocol will be reported following Standard Protocol Items: Recommendations for Interventional Trials (SPIRIT) statement (Additional file 1).

**Fig. 1 Fig1:**
[figure not shown]
Flowchart of the study design. KOA, knee osteoarthritis

**Fig. 2 Fig2:**
[figure not shown]
Schedule of enrollment, intervention, and assessment. NRS, Numerical rating scale; WOMAC, Western Ontario and McMaster Universities Osteoarthritis Index; STAI-S, State-Trait Anxiety Scale-State Anxiety Subscale; SETS, Stanford Expectations of Treatment Scale; fMRI, functional magnetic resonance imaging

### Study setting and recruitment

The study will be carried out at the Dongzhimen Hospital Affiliated to Beijing University of Chinese Medicine. The study will recruit participants with KOA who meet the diagnostic criteria of the American College of Rheumatology criteria [36] through hospital outpatient, WeChat official account (one of china’s popular social media platforms) of Dongzhimen Hospital and brochures. Meanwhile, the recruitment of participants has started in October 2019.

### Participants

#### Inclusion criteria

(1) Age between 45 and 65 years old, and gender is not limited; (2) knee pain lasts at least 6 months; (3) KL (Kellgren-Lawrence) grade II or III in recent 12 months; (4) numerical rating scale (NRS) ≥ 4 in the past week; (5) right handedness; and (6) signed informed consent.

#### Exclusion criteria

(1) History of knee replacement or waiting surgery (knee replacement or knee arthroscopy); (2) history of arthroscopy within 1 year or intra-articular injection within 6 months; (3) discomfort of knee joint caused by other reasons (such as joint cavity effusion, infection, malignant tumor, autoimmune disease, trauma, etc.); (4) serious organic pathological changes, mental abnormalities, and psychiatric or neurological disorders; (5) coagulation disorders; (6) pregnant or lactating women; (7) MRI contraindications, such as claustrophobia, implanted with pacemaker and other metal products; (8) severe skull anatomical asymmetry or definite lesions were found in magnetic resonance scanning; (9) received acupuncture or massage treatment in recent 1 month; (10) allergy to needles and alcohol or fear to acupuncture; and (11) participated in other clinical studies in the past 3 months.

### Informed consent and participant safety

Participants will be required to sign an informed consent (Additional file 2) and have the same chance to receive appropriate treatment. During the treatment, any adverse events, such as panic, subcutaneous hematoma, and pain, should be informed to the study researchers, who are responsible for monitoring and recording the adverse events and reactions throughout the study. If the participants cannot tolerate these adverse reactions, acupuncture treatment will be discontinued and the participants will be withdrawn from the study. There is no anticipated harm and compensation for study participation.

### Randomization

In this study, KOA participants will be randomly divided into acupuncture group, sham acupuncture group, and waiting list group in a ratio of 1:1:1, with 30 participants in each group. The random sequence will be generated by an independent professional statistician ([name]) who is not involved in the study with the software SAS 9.3 (SAS Institute, Cary, NC, USA) using block randomization. The random numbers will be stored by a fixed non-involved person. When the eligible participants are randomly assigned, the random number will be told by the fixed person to the acupuncturists via a short message.

### Blinding

Due to the operation characteristics of acupuncture, the acupuncturists cannot be blinded who will be informed of the grouping of participants before treatment. Participants will be told that they will randomly receive one of the interventions after enrollment. To avoid communication, participants will be assigned to different rooms during the treatment. Since the participants assigned to waiting treatment do not have any intervention, it is impossible to blind them. The outcome evaluators and data statisticians will be blinded to the group allocation, and their responsibility is to collect and analyze the data.

### Sample size

According to previous neuroimaging studies, in order to calculate statistical power for group-level fMRI studies, a sample size of 12 participants were required to achieve 80% power at the single voxel level when *α* = 0.05, and about 25 participants were required for a stricter threshold of *α* = 0.000002 [37, 38]. In this study, considering a 20% dropout rate and loss of data due to head motion, we plan to recruit 30 participants in each group. Each participant will receive 2 fMRI scans to explore different brain activity between the specific and nonspecific effects of acupuncture.

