### Statistical analysis

#### Clinical data analysis

The clinical data will be statistically analyzed by SPSS software (SPSS V.22.0 KO for Windows). Data will be described utilizing the mean (standard deviation) when following a normality assumption and using the median (quartile spacing) when the normality assumption is violated. The percentage (*n* %) will be used to describe the categorical variables. Comparisons between the three groups will be made by repeated-measures analysis of variance or Wilcoxon rank-sum (if normality is violated). For the primary outcome, we will calculate response rates at 4 weeks using the chi-square test. For the secondary outcomes, the mixed effect model and repeated measurement method will be used to compare the continuous variables (including WOMAC, SETS, and STAI-S).

The primary outcome will be performed using the intention-to-treat (ITT) and per-protocol (PP) analysis. ITT is defined as all randomized participants completing at least one post-baseline measurement. PP is defined as all the randomized participants who will not stop treatment prematurely, and complete 4 weeks of treatment, and undergo two MRI scans. The last observation carried forward (LOCF) will be used to estimate the missing values. The data will be considered statistically significant with a level of 0.05, and all hypothesis tests will be two-tailed.

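### Sample size: read plainly, 12 participants at α = 0.05 and about 25 at α = 0.000002 cannot share one effect and 80% power; 25 would have roughly 6–24%

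*Protocol article*

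**What the plan says.** The whole justification for the trial's size is in the protocol article under Sample size. It takes its figures from the literature ("According to previous neuroimaging studies, in order to calculate statistical power for group-level fMRI studies"). It states that "a sample size of 12 participants were required to achieve 80% power at the single voxel level when" α = 0.05, and in the same sentence that "about 25 participants were required for a stricter threshold of" α = 0.000002. The text then allows for 20% dropout and for data lost to head motion, and arrives at 30 per group.

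The section prints no effect size, variance, test or sidedness. It attaches 80% power to the first figure and mentions no other power, effect or design for the second. Elsewhere, Clinical data analysis says that "all hypothesis tests will be two-tailed". The Background gives the imaging aims as two between-group contrasts: true versus sham acupuncture, and sham acupuncture versus waiting list.

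**The concern.** Moving from α = 0.05 to α = 0.000002 is a 25,000-fold tightening, yet the requirement only about doubles, from 12 to 25. For a fixed effect and fixed power, the required number should rise about four- to fivefold.

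The second figure matters because it appears to drive the design: no other printed number leads naturally to 30 per group. A reader would conclude that about 25 evaluable participants give 80% power at a very strict voxel threshold for an effect that 12 participants can detect at 0.05. If that is untrue, an empty map for either contrast could be read as absence of a brain effect when the study had little chance of showing one. The trial is aimed at the debate over whether acupuncture differs from placebo, so that misreading would be costly.

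**Working it through.** **Inputs from the Sample size section:** n = 12, power 80%, α = 0.05; n = about 25, α = 0.000002; 20% loss; 30 per group.

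**Assumptions, because the text gives nothing:** one common standardised effect d; 80% power for both figures; test and sidedness unknown, so several were tried.

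**1. Normal approximation.** Required n is proportional to (z_α + z_β)², so the effect and SD cancel in the ratio. With z_β = 0.842:
- Two-sided: ((4.753 + 0.842)/(1.960 + 0.842))² = 3.99, and 12 × 3.99 = 47.9, so 48.
- One-sided: ((4.611 + 0.842)/(1.645 + 0.842))² = 4.81, and 12 × 4.81 = 57.7, so 58.

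Power at n = 25 is Φ[(z_0.05 + z_β)·√(25/12) − z_strict]:
- Two-sided: Φ(4.044 − 4.753) = 23.9%.
- One-sided: Φ(3.589 − 4.611) = 15.3%.

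**2. Noncentral t.** Power = P(T′ > t critical). One-sample: df = n − 1, noncentrality d√n. Two-sample with n per group: df = 2n − 2, noncentrality d√(n/2). Solve for d at n = 12, α = 0.05, 80% power, then apply that d at α = 0.000002.

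| Test | Sides | d from n = 12 | Power at n = 25 | n for 80% |
|---|---|---|---|---|
| One-sample t | 1 | 0.766 | 5.9% | 61 |
| One-sample t | 2 | 0.889 | 10.0% | 51 |
| Two-sample t, per group | 1 | 1.048 | 9.6% | 60 |
| Two-sample t, per group | 2 | 1.197 | 15.8% | 50 |
| z | 1 | 0.718 (one-sample) | 15.3% | 58 |
| z | 2 | 0.809 (one-sample) | 23.9% | 48 |

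The printed 25 is not reproduced by any of these.

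**3. Allowances.** Let sidedness differ between the two figures, and let the 12 be rounded up from an effect for which 11 already suffice.
- Least favourable: one-sample t, one-sided and then two-sided. Power is 4.0% and n = 65.
- Most favourable: z, two-sided and then one-sided, effect set at 11. Power is 34.9% and n = 42.

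Reading 12 and 25 as two-arm totals leaves the power within about 4–35%.

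**4. Reverse check.** For 25 to give 80% power at α = 0.000002, d must be 1.40–1.46 (one-sample t) or 1.73–1.79 (two-sample t). Such an effect would need only 5–7 participants at α = 0.05, and 12 would already have about 99% power or more.

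**5. Link to 30.** 25 × 1.2 = 30, and 24/0.8 = 30. Strict inflation of 25 gives 25/0.8 = 31.25, so 32. Starting from 12 gives 12/0.8 = 15. So 30 fits a figure of about 24–25, but the text does not show the step.

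**6. What the planned size can support (two-sample t, 80% power).** For d = 1.05–1.20, 25 per group reach 80% only at an uncorrected α of 0.0033 (one-sided) or 0.0015 (two-sided). At α = 0.000002 they need d = 1.73 or 1.79. With 24 per group (30 × 0.8), the same formulas give α of 0.0040 or 0.0020, and d of 1.78 or 1.84.

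**The case against.** The strongest reply is that the protocol article derives nothing here. It reports two figures from two cited studies, and the 80% is attached to the first only. If the sources used a different effect, variance or power for the second figure, both could be correct where they were published. This stands, and it makes the finding conditional. A reader might infer that the cited studies are wrong or that the 25 is a proven arithmetic error. The document cannot support that, because it prints too few inputs and the sources are not at hand. What remains is that the sentence changes only the threshold, so if another condition also changed, the condition that makes 25 valid has been left out.

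A second reply is that no planned analysis is fixed at α = 0.000002. Neuroimaging data analysis names no voxel threshold, and the only level stated in the clinical analysis is 0.05. This also stands. A reader might infer that the trial's imaging analysis has 6–24% power. The documents do not say so: that range describes the claim in the sample-size sentence, not a specified test. Nor is 24% a strict upper limit, since the allowances reach about 35%.

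Third, the imaging work is framed as exploratory, and the Discussion concedes that the small groups limit what can be concluded. That softens the risk of misreading an empty map, but it does not correct the figure. Finally, the step from 25 to 30 is an inference from arithmetic, and is treated as one here.

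**Conclusion.** The point holds in conditional form. If one effect and 80% power underlie both figures, the 12 and the 25 are incompatible under every standard test tried: power at 25 is about 6–24% with matched tests and about 4–35% with generous allowances, against the 80% a reader would assume. The required number is about 48–61 (42–65 with the allowances), not 25.

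The result rests on the plain reading of one sentence. It does not depend on the size of the common effect under the normal approximation, and only slightly on the choice of test. It does not show that 30 per group is the wrong number to recruit, and it has no bearing on the clinical primary outcome. The paragraph should be corrected because it is the only sample-size justification printed and it suggests a sensitivity that its own figures do not deliver.

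**What to change.** Keep 30 per group and rewrite the paragraph:

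- Check the two cited sources. Either print the effect, variance, test, sidedness and power that make about 25 valid at α = 0.000002, or withdraw that claim.
- State what the expected number of evaluable participants can detect with 80% power in the planned between-group contrasts, using a two-sample test. At 25 per group, this is the effect implied by 12 per group (d of about 1.05–1.20) only at an uncorrected voxel α of about 0.0015–0.0033, or d of about 1.73–1.79 at α = 0.000002. If 24 per group is taken as the expected number, use the slightly less favourable values worked out above. One-sample effects should not be used here, because they would overstate sensitivity for the true-versus-sham and sham-versus-waiting-list contrasts.
- Show the step from the evaluable number to 30.
- Add that failing to detect a difference at a strict corrected threshold is not evidence of no brain effect.

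The cost is one paragraph and a look at two references, with no extra participants or scans. The downside is that the stated imaging sensitivity becomes less favourable.

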### Clinical outcome assessments

The primary outcome will be the response rate, which is defined as a decrease of more than 2 points on the NRS at week 4 compared with baseline [39]. NRS is a line divided into 10 segments. The degree of pain is assessed by 0–10 scores, and 0 score represents pain-free and 10 score represents the worst pain.

The secondary outcomes will be as following: (1) Pain subscale of Western Ontario and McMaster Osteoarthritis Index (WOMAC) scale will be used to evaluate the degree of knee pain of the participants. (2) Function subscale of the WOMAC scale will be used to evaluate the knee joint function. (3) Stiffness subscale of WOMAC will be used to evaluate the stiffness of knee joint. The severity of knee joint will increase with the higher scores of WOMAC. Participants will fill out the WOMAC scale at weeks 0, 2, and 4. (4) Blinding assessment and rescue medicine. (5) Stanford Expectations of Treatment Scale (SETS) will be used to assess participants’ positive and negative expectations of the upcoming treatment and their overall understanding of the purpose of the treatment. Participants will be asked to fill out the SETS scale before weekly treatment. (6) State-Trait Anxiety Scale-State Anxiety Subscale (STAI-S) will be used to evaluate the severity of current anxiety symptoms in participants with knee osteoarthritis. Participants will fill out the STAI-S scale at weeks 0, 2, and 4.

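### The only sample-size basis is single-voxel fMRI power, which does not support the primary response-rate comparison; as a minor point, 30 per group less 20% leaves 24, just under the cited figure of about 25

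*Protocol article*

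**What the plan says.** The Sample size section of the protocol article relies on earlier neuroimaging work. At α = 0.05, "a sample size of 12 participants were required to achieve 80% power at the single voxel level"; at α = 0.000002, "about 25 participants were required for a stricter threshold of" that value. It then sets the trial's size: "considering a 20% dropout rate and loss of data due to head motion, we plan to recruit 30 participants in each group". It gives no effect size, does not say whether 12 and 25 are one-sample or per-group numbers, and gives no response rates, difference or power for a clinical endpoint.

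The section Clinical outcome assessments states: "The primary outcome will be the response rate", a yes/no outcome based on the fall in NRS pain at week 4. Clinical data analysis assigns it a chi-square test at a two-sided 0.05 level, with ITT and per-protocol sets and LOCF for missing values. Only the per-protocol set requires both MRI scans. The Background defines the effects of interest as between-group contrasts: acupuncture versus sham (specific) and sham versus waiting list (nonspecific). Allocation is "in a ratio of 1:1:1, with 30 participants in each group". The Discussion lists the small group size as a limitation, without a figure.

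**The concern.** The article offers a reason for 30 per group, and that reason belongs to a different endpoint from the one named primary. Power to detect a signal in one voxel says nothing about a difference between two proportions. This is not a detail left to a document we cannot see: the article states a rationale for its size, and that rationale does not reach the primary comparison.

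The contrast most exposed is acupuncture versus sham. The Abstract opens with the debate over whether acupuncture is equivalent to placebo. A trial of this size can easily return p>0.05 on that contrast while a large difference remains possible.

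The section's own figures also do not quite meet. After the stated 20% loss, 30 recruited does not leave 25.

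**Working it through.** **Step 1. How 30 was reached.** Inputs from Sample size: reference sizes 12 and about 25, loss 20%, 30 recruited per group.

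- From 12: 12 × 1.2 = 14.4 and 12/0.8 = 15, so 15 after rounding up either way. This does not lead to 30.
- From 25: 25 × 1.2 = 30, which reproduces the plan's figure exactly. So 25 is evidently the base, although the section never expressly adopts it.
- Correct inflation is n/(1 − loss): 25/0.80 = 31.25, rounded up to 32 per group (96 in total).
- As planned: 30 × 0.80 = 24 per group (72 of 90), one short of 25.
- Largest loss that still leaves 25: 1 − 25/30 = 16.7%.

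The wording "considering a 20% dropout rate and loss of data due to head motion" can mean that head motion is inside the 20% or on top of it. Only the second reading enlarges the shortfall.

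**Step 2. What 30 per group gives the primary outcome.** The article states no response rates, so comparator rates of 20%, 30%, 40% and 50% are assumed. The test is the uncorrected chi-square for two groups at two-sided 0.05, without multiplicity adjustment. Power is the sum, over all pairs of responder counts, of the two binomial probabilities for the pairs at which the test rejects.

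| Comparator rate (assumed) | 30/group: rate giving 80% power | Difference | Power for +20 points | 24/group: rate giving 80% power | Difference | Power for +20 points |
|---|---|---|---|---|---|---|
| 20% | 54.5% | 34.5 | 39% | 58.0% | 38.0 | 33% |
| 30% | 65.5% | 35.5 | 35% | 68.5% | 38.5 | 31% |
| 40% | 75.0% | 35.0 | 35% | 78.0% | 38.0 | 31% |
| 50% | 83.5% | 33.5 | 35% | 86.5% | 36.5 | 31% |

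In round terms, 34–36 points and 35–39% power at 30 per group, and 37–39 points and 31–33% at 24 per group. The usual normal formula agrees closely: 33–35 points at 30 per group, and 93 per group needed to detect 70% versus 50% with 80% power.

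Precision at 30 per group, with assumed rates of 60% and 50%: the 95% CI half-width is 1.96 × √(0.6 × 0.4/30 + 0.5 × 0.5/30) = 0.25, or about ±25 points.

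**Step 3. What 25 gives a two-group imaging contrast.** The section does not say which design 25 describes, so both readings are worked with the noncentral t distribution at two-sided α = 0.000002. The standardised effect d is the one that gives 80% power at 25.

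| Assumption about 25 | Implied d | Two-group power, 24/group | Two-group power, 30/group |
|---|---|---|---|
| One-sample figure | 1.46 | 38% | 63% |
| Per-group figure, two-sample test | 1.79 | 76% | 93% |

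Under the one-sample reading, a one-sample test at n = 24 has 75% power, and a two-group contrast needs about 36 per group for 80%.

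At the looser threshold (α = 0.05, reference size 12 read as one-sample, d = 0.89), a two-group contrast has 85% power at 24 per group and 92% at 30.

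**The case against.** Several points on the other side are sound.

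- The shortfall is one participant per group against an approximate figure, and the section quotes 25 from earlier work without committing to the stricter threshold. On its own, this is a wording correction.
- A reader might infer that 12 and 25 are single-group or total numbers, so that the imaging contrasts are badly underpowered. The article does not say so; it speaks only of group-level fMRI studies. The per-group reading is equally open and gives 76–93%, and at α = 0.05 the power is adequate even under the one-sample reading.
- A reader might infer that head-motion loss comes on top of the 20%. The wording allows either reading.
- A reader might apply 24 per group to the primary outcome. The ITT set with LOCF keeps any randomised participant with one post-baseline measurement, and head motion removes images, not NRS scores. The 30-per-group figures are therefore the main ones, and those at 24 are a lower case.
- The article does not say that a non-significant result will be taken as equivalence. It describes a debate, presents the study as exploratory, and concedes that the groups are small.

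These points reduce the arithmetic to a minor note and lower the severity. They leave the main point standing: the stated size has no connection to the outcome declared primary, and the general remark about small groups gives no detectable difference.

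**Conclusion.** The concern holds, with the weight on the primary outcome. The only sample-size basis is single-voxel fMRI power, and it does not support a chi-square comparison of response rates. At 30 per group, the trial has 80% power only for a difference of about 35 points. This rests on assumed comparator rates of 20–50% and unadjusted pairwise tests at two-sided 0.05.

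The arithmetic slip is real but minor: 24 against about 25, with a tolerable loss of 16.7% instead of 20%. The documents do not support a firm statement that the imaging contrasts are underpowered, because that depends on which design the cited 25 describes. This should be fixed, but it does not undermine the trial.

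**What to change.** Amend the text without enrolling more participants.

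1. In Sample size, state that 30 per group leaves about 24 evaluable for imaging if 20% are lost, slightly below 25, and say whether head-motion loss is inside the 20%.
2. State which design the cited 12 and 25 refer to, after checking the sources. Do not assert that they are single-group figures unless the sources say so.
3. State that the sample size was not derived for the response rate, and give its detectable difference: about 35 percentage points at 30 per group for 80% power at two-sided 0.05, with the assumed comparator rates.
4. In Clinical data analysis, report the acupuncture-versus-sham risk difference with a 95% CI, and state that p>0.05 will not be read as equivalence.

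The cost is a few sentences and no extra participants. The downside is that the stated figures become less favourable.
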